#### Interim analyses

Interim analyses will be conducted by the data analyst who is otherwise masked to intervention allocation.

#### Methods for additional analyses (e.g., subgroup analyses)

The baseline characteristics of participants in all arms at the cluster level and individual-level characteristics at baseline and endline will be compared using Student’s *t* test and hierarchical or mixed-effect models to estimate the ratio of these means. As the ODs have several health centers, we will adopt a linear mixed-effects model adjusting for baseline measurements to account for clustering in the data. Individual-level data will also be incorporated into multivariable regression models to account for potential confounders differing by the trial arm and improve the precision of the risk ratios by accounting for intercluster variations.

#### Methods in analysis to handle protocol nonadherence and any statistical methods to handle missing data

We will adopt intention-to-treat analyses, and imputation methods will be considered in the event of missing data.

#### Plans to give access to the full protocol, participant-level data, and statistical code

Information from the full protocol will be published in a peer-reviewed journal. The relevant data analyzed during the development of this study protocol are available upon request from the corresponding author.

### Oversight and monitoring

#### Composition of the coordinating center and trial steering committee

The coordinating center will be based in the KHANA Center for Population Health Research. The steering committee will comprise representatives from CATA, CENAT, KHANA, and Saw Swee Hock School of Public Health, National University of Singapore. Data will be managed by the team at KHANA, with inputs from the other two implementing organizations. The research team from Saw Swee Hock School of Public Health, National University of Singapore will be responsible for the analyses of the data from the trial. The steering committee will adjudicate the endpoints and develop the findings dissemination plan in consultation with the data monitoring committee.

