#### Strategies to improve adherence to interventions

In this study, the implementing organizations will design and ensure that the interventions’ (TB case-finding) protocols are strictly adhered. The medical procedures and laboratory tests (e.g., GeneXpert, CXR, and sputum microscopy) conducted in this study are in accordance with the national TB guidelines. In addition, the National University of Singapore, which is not an implementing organization, will conduct regular field visits and interim analyses to ensure adherence to study protocol.

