### Sample size

Simulations were conducted to estimate the power of the trial to detect a statistically significant difference between the intervention arms and the control arm for the primary outcome of the trial. To develop a basis for these simulations, we examined the ranges and variability of effect sizes from previously collected data that included operations data from CATA, CENAT, KHANA, and the NTP annual TB report 2018 [28]. We defined effect size as the percentage increase in the number of cases notified to the NTP because of the intervention (baseline: PCF). CATA, CENAT, and KHANA have implemented the respective interventions (different strategies of ACF) at different sites in Cambodia between 2017 and 2018. The percentage of estimated additional cases notified to the NTP by CATA, KHANA, and CENAT during the intervention period (scenario 1) was 110%, 98%, and 30%, respectively. For this scenario, the power was over 90%. We also considered three more sets of conservative effect sizes: (scenario 2) assuming all intervention arms have an effect size of 75%; (scenario 3) assuming all intervention arms have an effect size of 50%; and (scenario 4) assuming all intervention arms have an effect size of 25%. There was a similar level of power for a more cautious estimate (scenario 2—a 75% improvement in case notification). In scenarios 3 and 4, the power was maintained above 70% that a difference between intervention and control arms could be detected.

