#### Procedure for unblinding if needed

This pragmatic cluster randomized trial is open-label, where project coordinators and staff are not blinded. All case-finding activities will be implemented in the selected sites, as indicated. Study participants and health center/laboratory staff will not be notified if they are part of the intervention group or the control group. Therefore, unblinding will not occur in this trial.

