### Data collection and management

#### Plans for assessment and collection of outcomes

For the primary endpoints, we will collect case notification data from the intervention implementers (CATA, KHANA, CENAT), the provincial health department, and health centers (Table 2). For the secondary endpoints, data on treatment outcomes will be collected from the health centers. To assess the number needed to screen, we will collect screening data and the number of TB cases diagnosed from the intervention implementers, the provincial health department, and health centers. Data on costs—direct and indirect medical costs [29, 30], intervention, diagnostics, and medications—will be collected from the intervention implementers and the baseline and follow-up surveys (Table 2). In the survey, we will document the baseline characteristics of new diagnoses found in all arms using a questionnaire. Information on age, gender, education level, occupation, number of family members and housing, smoking, alcohol use, drug use, TB history, and the presence of other comorbidities will be collected. We will adapt and contextualize the knowledge, attitude, and practice survey instrument tools developed by the WHO to collect information on TB knowledge, attitudes, and care-seeking behavior toward TB [31]. A short follow-up survey will be conducted at the end of the TB treatment period for each person with TB to collect information on missed doses, side effects, and other TB treatment-related costs incurred.

**Table 2 Tab2:** Endpoints and data collection

Study endpoint	Description	Data source
Primary endpoints		
Case notification rates (cases notified per 10,000 population per year)	Numerator: number of cases notified by the selected districts	Case notification data from CENAT
	Denominator: total population in the OD	Population statistics (Ministry of Planning/Department of Statistics/CENAT)
Additionality (additional number of cases reported compared to historical baseline)	Number of cases notified by the selected districts	Case notification data from CENAT
	Historical data (cases notified in the preceding 3 years)	Historical case notification data from CENAT
Cumulative yield (cases diagnosed per 1000 screened)	Numerator: number of cases reported by each arm	Program data In the control arm, data to be collected from the health centers monthly

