#### Composition of the data monitoring committee, its role, and the reporting structure

The data monitoring committee (DMC) will comprise representatives from KHANA Center for Population Health Research and Saw Swee Hock School of Public Health, National University of Singapore. The DMC will be formed independently from the funders. The DMC will be responsible for the independent assessment of the validity and integrity of the pragmatic cluster randomized controlled trial. Interim analyses will be presented to the DMC. The DMC will report trial progress and the results of the trial steering committee. The DMC will meet twice a year, or more if needed.

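### Endpoint adjudication is given to a steering committee with an implementer majority and no stated masking, and the DMC's membership does not support the independence claimed for it

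*Protocol article*

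**What the plan says.** The section on the coordinating center and trial steering committee gives membership and powers together. On membership: "The steering committee will comprise representatives from CATA, CENAT, KHANA, and Saw Swee Hock School of Public Health, National University of Singapore". On powers: "The steering committee will adjudicate the endpoints and develop the findings dissemination plan in consultation with the data monitoring committee". It also places the coordinating center in KHANA's research center, gives data management to KHANA and gives the analysis to the university school.

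The section on collection of outcomes identifies the implementers: "we will collect case notification data from the intervention implementers (CATA, KHANA, CENAT), the provincial health department, and health centers". The Sample size section links each of them to its own model: "CATA, CENAT, and KHANA have implemented the respective interventions (different strategies of ACF) at different sites in Cambodia between 2017 and 2018". The section on adherence separates out the remaining member: "the National University of Singapore, which is not an implementing organization, will conduct regular field visits and interim analyses".

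On masking, the section on unblinding says: "This pragmatic cluster randomized trial is open-label, where project coordinators and staff are not blinded". The section on who will be blinded lists the data analysts and nobody else.

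On oversight, the DMC section says: "The DMC will be responsible for the independent assessment of the validity and integrity of the pragmatic cluster randomized controlled trial". Its members are to come from KHANA's research center and the university school. The only separation it states is from the funders.

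**The concern.** A TB case, as defined under Outcomes, need not be bacteriologically confirmed. It may be smear-negative disease accepted by a clinician on an abnormal X-ray or a failed antibiotic course, or extrapulmonary disease recognised from local and general symptoms. Those two categories involve judgement.

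If a body has the power to adjudicate such an endpoint in an open-label trial, its members should either not know the arm or have no interest in the result. The article gives the power to a committee for which it states neither safeguard. What is at stake is the credibility of the comparison between ACF and PCF, and of the comparisons among the three ACF models, since each implementer is tied to one of them.

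The DMC would be the natural check, and interim analyses are presented to it. It is drawn from organisations already on the steering committee, so the independence claimed for its assessment is not supplied by its membership.

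**Working it through.** No formula applies and there is no stated figure to reproduce. The check is a cross-reading of sections and a count of memberships.

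1. **Steering committee.** Member bodies: CATA, CENAT, KHANA and the university school. Bodies named as intervention implementers: CATA, KHANA and CENAT. Implementers on the adjudicating committee: 3 of 4.

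2. **DMC.** Member bodies: KHANA's research center and the university school. Organisations that implement an ACF arm: 1 of 2 (KHANA). Organisations also on the steering committee: 2 of 2. Organisations with another operating role in the trial: 2 of 2. KHANA hosts the coordinating center and manages the data; the university school analyses them.

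3. **Masking.** Project coordinators and staff are unblinded. Data analysts are masked. Participants and health center and laboratory staff are not told their group. No section masks the steering committee. That its representatives know the allocation is an inference: the article does not say so of the committee, but an organisation running case finding in particular districts can be expected to know which districts they are.

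4. **Scope for judgement.** The case definition admits clinically diagnosed smear-negative and symptom-based extrapulmonary disease. The article does not give their share of all cases.

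5. **Where the counts come from.** Diagnoses are made by clinicians. Under Outcomes, cases are ascertained from screening results and routine notifications to the NTP, with data collected on aggregated forms or as reported by the implementation teams. Table 2 takes the numerator of the case notification rate from CENAT's notification data, and the Statistical methods section divides that count by district population. For cumulative yield, Table 2 takes the numerator from program data on cases reported by each arm.

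6. **Putting 1 to 5 together.** The power to adjudicate is stated, the implementer majority is stated, and no masking of that body is stated. The counting rules describe no step at which the power would be used. The governance text and the counting rules therefore do not fit: either adjudication can change the counts, in which case it rests with interested parties, or it cannot, in which case the sentence should not be there.

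**The case against.** The strongest reply is that the sentence has no operational content. The article describes no case listing, no review procedure and no rule for overturning a diagnosis. Clinicians diagnose, health centers and implementers report, the NTP records, and the rate is computed from aggregate counts. A committee handed aggregates has no individual smear-negative case to accept or reject, and the verb may mean no more than agreeing the endpoint data. Health center and laboratory staff, who are closer to routine diagnosis, are not told the group. The three implementers run competing models, so they are not one bloc with one interest. An adjudication procedure or DMC charter may also sit in the full protocol.

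Much of this stands. It limits the size of the problem, and the lack of a described procedure is not itself the point. It does not dispose of what the article affirmatively states: who adjudicates, who sits on that body, and that the DMC's assessment is independent.

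A reader might infer that implementers will decide borderline cases one by one and so shift the ratio of ACF to PCF cases by a definite amount. The documents do not support that. They describe no case-level decision, and give neither the share of clinically diagnosed cases nor any figure for how far knowledge of the arm would alter their acceptance.

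A reader might also suppose that the remedy is to pass adjudication to the university as the non-implementing member, or simply to take KHANA off the DMC. Neither delivers independence. The university analyses the trial, makes regular field visits that could reveal which district runs which arm, and sits on the DMC itself.

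**Conclusion.** The point holds as a governance defect in stated text. Endpoint adjudication is assigned to a committee on which 3 of 4 bodies deliver ACF arms, with no masking of that committee, in an open-label trial whose case definition is partly clinical. Separately, the independent assessment promised of the DMC is not delivered by a membership made up of an implementer's research center and the analysing school, both organisations being on the steering committee.

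The size of any bias cannot be derived from the document and may be small, because the primary count rests on clinicians' diagnoses and routine notifications. The conclusion assumes that adjudication carries its ordinary meaning and that committee representatives know which districts their own organisations serve. It does not establish that any count would be altered. It shows an avoidable route to bias that can be closed by a change of wording.

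**What to change.** In the steering committee section, delete adjudication of the endpoints from the committee's tasks. State instead that cases are counted as registered with the NTP under the case definition given in Outcomes, without adjudication. If review of a disputed case cannot be avoided, state that it is done by people outside the implementing organisations, on listings from which district and arm have been removed.

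In the DMC section, describe the committee as independent of the funders only and drop the claim that its assessment is independent. The claim can stay if members are drawn from outside both the implementers and the analysis team.

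The counting rule largely matches what Outcomes, Table 2 and the Statistical methods section already specify for the notification rate, so the change is mainly one of wording. The cost is that implementers lose a direct say on disputed cases; masked listings are needed only if review is kept, and new members only if the DMC claim is kept. One limit remains. The rule removes the committee's power over the counts, but implementers still report the cases used for cumulative yield, as Table 2 provides.

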#### Composition of the data monitoring committee, its role, and the reporting structure

The data monitoring committee (DMC) will comprise representatives from KHANA Center for Population Health Research and Saw Swee Hock School of Public Health, National University of Singapore. The DMC will be formed independently from the funders. The DMC will be responsible for the independent assessment of the validity and integrity of the pragmatic cluster randomized controlled trial. Interim analyses will be presented to the DMC. The DMC will report trial progress and the results of the trial steering committee. The DMC will meet twice a year, or more if needed.

#### Adverse event reporting and harms

There are no major perceivable risks in this study. The potential psychological distress because of the questions that the study poses is minimal. Participation is purely voluntary, and the decision to not participate in this study or to terminate their participation at any point during the study will not have any negative consequences. All participants and those who refuse to partake in the survey will not be deprived of the standard care they ought to receive for TB. As the interventions we are evaluating are operations that have been implemented and endorsed by the NTP, the risks have been thoroughly deliberated. The interventions involve only models of care to reach people with TB. TB screening, diagnosis, and treatment algorithms included in these models are per standard protocol in Cambodia.

#### Frequency and plans for auditing trial conduct

The research team will conduct at least two monitoring visits to each OD during the 1-year implementation period. Field supervisors will also conduct at least four monitoring visits (e.g., every quarter for KHANA arms where the intervention is spread over 1 year and at every screening session conducted by CATA and CENAT during the implementation period, respectively). During monitoring visits, we will review consent forms, completeness of the data collection forms, and compliance with the trial protocol. Any anomalies in recruitment and data will be followed up by the field staff. Interim analyses will be conducted by the data analyst who is otherwise masked to intervention allocation. Data, recruitment processes, and interim results will be monitored by the research team and reported to the DMC.

#### Plans for communicating important protocol amendments to relevant parties (e.g., trial participants, ethical committees)

Amendments to the protocol will be duly communicated to all relevant parties, including the NTP and all partners, investigators, ethics boards in Cambodia and Singapore, the trial registry, and journals.

#### Dissemination plans

We will share the findings from this study in results dissemination meetings with key stakeholders and peer-reviewed journals. Findings from this trial could also potentially inform ACF strategies in other countries with a high TB burden.

## Discussion

In partnership with CATA, CENAT, and KHANA, this pragmatic cluster randomized controlled trial seeks to examine the effect of community-based ACF strategies in increasing TB case detection and its impact on treatment outcome. This trial focuses on the ACF approaches, which are currently adopted as one of the mainstay strategies to promote early TB diagnosis in Cambodia [37, 38]. We will undertake a pragmatic approach [39] by testing existing interventions against usual care (PCF) in a setting where these interventions have been previously conducted to enhance generalizability and replicability in Cambodia and other similar settings in the future.

KAPs at risk for TB, such as people living with HIV, close contacts of people with TB, and persons aged 55 years and older [18], are often those with limited access to health care, leading to a delay in TB diagnosis and poor clinical outcome [40] and further transmission of the infection in the community [41]. Therefore, the prioritization of high-risk groups for systematic screening of TB has been identified as a key component in the global efforts to end TB [26]. However, ACF activities can be costly [42], and a rigorous assessment of cost-effective ACF strategies is therefore a critical justification for TB control program planning and scale-up in a high-burden, often resource-poor setting. Also, the implementation of this project will complement TB control programs in Cambodia by expanding ACF to ODs that are currently not served by CENAT, and other implementing organizations, thus rendering operation and strategic benefits to the country’s efforts to find undiagnosed TB cases in the community. It will also contribute to the capacity-building of local staff in research.

An important foreseen limitation of our study is that we will not be able to determine the impact of ACF on the prevalence of TB in Cambodia. However, we believe that the primary and secondary endpoints of this study will generate an evidence base that is relevant to Cambodia and generalizable beyond this research setting.

This project is congruent with the global plan to end TB [43] by informing sustainable and evidence-based solutions for TB control in Cambodia. Upon completion of this trial, the results will inform and enable a nationwide scale-up of an effective intervention that is contextualized and complies with the principles set by the NTP to find undiagnosed cases and control TB in Cambodia.

## Trial status

Protocol version 1, December 3, 2019. Recruitment began on December 18, 2019 and will be completed by approximately December 31, 2020.

## Data Availability

Data sharing is not applicable to this article as no datasets were generated or analyzed during the current study. However, any data required to support the development of this protocol can be supplied upon request.

## Abbreviations

ACF: Active case finding
CATA: Cambodia Anti-Tuberculosis Association
CENAT: National Center for Tuberculosis and Leprosy Control
CI: Confidence interval
CXR: Chest X-ray
DMC: Data monitoring committee
HIV: Human immunodeficiency virus
ICER: Incremental cost-effectiveness ratio
KAP: Key affected population
NIHA: National University of Singapore Initiative to Improve Health in Asia
NTP: National tuberculosis program
OD: Operational districts
PCF: Passive case finding
TB: Tuberculosis
USD: US dollar
WHO: World Health Organization
